## **8.1. Vaccine logistics circuit**

The purchase of vaccines administered as part of the PrevHPV - Facilitation of Access intervention (Gardasil9®, injectable suspension in pre-filled syringe Laboratoires MSD Vaccins) will be carried out in accordance with the procedures of the public procurement code, defined according to the overall cost of the vaccines. The purchase and supply of vaccines will be carried out and under the responsibility of one (or more) Pharmacy(ies) for In-house Use (PUI) of the participating regions, or failing that by a pharmaceutical service provider. For each middle school benefiting from the 'Facilitation of access' component, the middle school referent and the PrevHPV project manager of the region concerned will define the number of vaccines to be provided according to the feedback from vaccination consent forms. The vaccines will be sent to each vaccination center concerned a few days before the middle school vaccination day. On the day of the middle school vaccination, the mobile team from the vaccination center will transport the vaccines previously received. All vaccine deliveries (between the supplier and the PUI, between the PUI and the vaccination centers, between the vaccination centers and the middle schools) will respect the cold chain.

There will be no specific packaging and/or labeling of the vaccines as the vaccine itself is not the subject of the research. The present research aims to evaluate the effect on vaccination coverage of a change in access to vaccination, the vaccine in question having a marketing authorization for the population targeted by the study.

The entire drug circuit (purchase, supply to PUIs and vaccination centers, storage, transport to middle schools) will comply with current pharmaceutical regulations.

The preparation and organization of vaccination days is the subject of a procedure. The vaccine circuit is currently being developed.

## **8.2. Allocation modalities**

### **8.2.1. Randomization**

Two successive randomizations are implemented:

- (i) A first randomization aimed at selecting 409 municipalities from the list of 2049 eligible municipalities, identified from the [data.education.gouv.fr](http://data.education.gouv.fr) site. For reasons of feasibility, different sampling fractions were applied for the municipalities of the departments in which the SC teams are located (1/2), the municipalities of other departments but belonging to the regions in which the SC teams are located (1/5), regional municipalities in which SC teams are not located (1/8).

- (ii) A second randomization aimed at assigning the assignment group (among the 6 in the research) to each of the 90 municipalities participating in the research (participation agreement for all middle schools). The 90 municipalities will be randomized concomitantly ('all at once').

These 2 randomizations are stratified on the department and the ecological indicator of deprivation (FDep) dichotomized into 2 classes (< or > median of eligible municipalities in the department). They are carried out by the EA APEMAC (University of Lorraine), using the SAS software version 9.4 (Proc RandomSampling).

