### **5.3. Selection methods**

Recruitment is carried out in two stages: (i) the selection of eligible municipalities, (ii) the selection of participating middle schools, making it possible to recruit the 90 municipalities, (iii) the randomization of the components of the intervention, and (iv) the identification of GPs to participate in the training.

1 Current vaccination recommendations (9-13) target girls and boys aged 11 to 14, with a catch-up possible from 15 to 19 years old. However, the vast majority of middle school students are between 11 and 14 years old. The exact age of middle school students on the planned date of the vaccine injection will be verified with the middle school administration. It is not possible to vaccinate middle school students under 11 years old, as this age is not indicated in the authorization for the vaccine.

2 The absence of HPV vaccination on the date of offer of vaccination in middle school will be verified with the parental authority at the time of the request for vaccination authorization, and checked against the health record at the time of injection.

3 The absence of contraindication to vaccination will be verified by the doctor of the vaccination center carrying out the injection on site at the time of the procedure, by questioning the student and checking the vaccination record.

4 Affiliation to a social security scheme will be verified with the middle school administration between the date of authorization from parental authority and the planned date of vaccination.

754 • **Selection of eligible municipalities:**

755 Information from academies (rectorates and diocesan management)

756 Each selected academy (rectorates and diocesan directorates) is informed in advance of the research by  
757 a note from the director of the DGESCO, and a letter detailing the experiment from the PrevHPV SC.

758 At the same time, 2049 municipalities in the selected academies meeting the inclusion criteria defined  
759 above were identified using data extracted from the data.education.gouv.fr website. These municipalities  
760 are then stratified according to the department and the FDep (ecological indicator of deprivation,  
761 dichotomized into 2 classes: > national average, < average). A random draw stratified on these two  
762 criteria made it possible to identify 409 potentially participating municipalities ([appendix 3](#)).  
763

764 • **Selection of participating middle schools:**

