765 For each of the 409 municipalities selected, the principals and directors of each middle school located in  
766 the municipality are contacted by telephone, after having been informed by mail of PrevHPV research.  
767 This telephone contact allows us to provide additional information on the research and to request the  
768 middle school's agreement (or not) to participate. Ultimately, the participating municipalities are those for  
769 which all the middle schools located there (public + private) agree to participate in the research. The total  
770 number of municipalities to recruit is 90. If this number is not reached after contacting the 409  
771 municipalities previously selected, a second stratified draw - using the same methods as the first - is  
772 carried out from the initial file of the 2049 (- 409) municipalities.  
773

774 The principals and directors of each middle school are informed that, depending on the results of the  
775 randomization of the intervention components, participating in the research may involve benefiting from:

776 (i) EMM + facilitation of access to vaccination,

777 (ii) EMM alone,

778 (iii) neither (control group),  
779

780 A commitment to respect the result of the randomization will be requested from the principals/directors of  
781 the participating middle schools, that is to say to facilitate the implementation of the EMM components  
782 and/or facilitation of access to vaccination if they are concerned.  
783

784 • **Randomization of intervention components:**

785 For each of the 90 participating municipalities, a random draw stratified on the department and the  
786 deprivation group (according to the FDep) makes it possible to randomly assign one of the 6 research  
787 groups to each municipality. At the end of this draw, the DGESCO, the rectorates and the diocesan  
788 management, as well as the principals and directors of the middle schools are informed by postal mail  
789 from the PrevHPV's SC of the components the middle school will benefit from.  
790

791 5 The list of municipalities cannot be established until the middle schools agreeing to participate are known. Due to the COVID-19 lockdown, organizational  
792 changes within middle schools following the end of lockdown, the upcoming summer holidays and potential changes of principals in middle schools at the next  

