## **11.2. Sample size calculation**

The sample size will depend on the number of participating middle schools, which is not known at this stage. This is why at this stage, we will consider the situation of a single middle school per municipality. The calculation below is therefore conservative.

According to government statistics, the number of students per middle school is on average 466. Assuming one middle school per cluster, the average size of the cluster would therefore be 466 adolescents aged 11 to 14. Twenty percent of middle schools having fewer than 300 students and 13% having more than 700, we retain a coefficient of variation of 0.5 in the size of the clusters.

The intra-class correlation coefficient is set at 0.05.

The current prevalence of initiation of vaccination from 11 to 14 years old is 16.1% among girls and 0% among boys due to the date of application of the HAS recommendation on the vaccination of boys. Girls representing 48.85% of the population in this age group, the prevalence among 11-14 year olds is 7.86%. The objective of the intervention is to increase this prevalence by at least 10% (based on data published in the literature). Considering two groups, we would need 15 clusters per group to reach a power of 90% and considering an alpha risk of 5%.

This research will include 6 groups, and the analysis will be carried out using a modeling approach in which several parameters will be tested: effects of interventions, and potential interactions between interventions. It is not planned to make multiple 2 to 2 comparisons. Therefore the alpha risk has not been corrected.

In the end, knowing that 6 groups will be formed, we plan to include a total of 90 municipalities (15 per group). This corresponds to an expected sample of 41,940 adolescents aged 11 to 14, under the assumption of a single middle school per municipality.

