### **11.3.1. Analysis of the primary outcome**

The prevalence of vaccination (at least 1 dose received and complete vaccination) among adolescents aged 11-14 is calculated (from SNDS data, supplemented where appropriate with data from vaccination centers, family planning centers and vaccines delivered in middle school) at the different measurement times (before intervention, 2 months, 6 months and 12 months after intervention) and in each of the six study groups. A calculation of this prevalence according to the sex and deprivation level of the municipality of residence of the adolescents is also planned.

Concerning the analysis of the primary outcome (vaccination coverage rate), an analysis at the cluster level will be carried out, that is to say that the unit of analysis will be the municipality and not the adolescent who is nested in his or her municipality. The data will be collected at the municipality level. Each municipality (= cluster) will be weighted by its size. A modeling approach will be used, carrying out a global analysis of the 90 randomization units. The model will be a linear model in which we will consider 3 fixed effects (one per component) and potential interactions between component. The baseline VC will be considered as an adjustment variable.

The evolution of the VC over time (M2, M6, M12) will also be modeled by considering a longitudinal model, and adjusting for the baseline VC rate.

Subgroup analyzes will be carried out according to sex, deprivation level (FDep) and considering a modeling approach with interaction terms.

Depending on the quality of the data reported by vaccination centers and family planning centers, sensitivity analyzes will be carried out to take into account only SNDS data and the number of vaccines delivered in middle school.

The analyzes are carried out using SAS software version 9.4 or later (SAS Institute Inc.) or R, and considering two-sided statistical tests and a level of significance of 5%.

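### Two FDep cut-points are given for the stratified draws, and the primary model as written adjusts for baseline coverage but not for the stratification factors

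*Protocol*

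**What the plan says.** **Selection draw.** Protocol section 5.3 describes the draw of 409 municipalities from 2049, stratified on department and on FDep "dichotomized into 2 classes: > national average, < average". It is reported in the past tense.

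**Allocation draw.** Section 5.3 stratifies the allocation of the 90 municipalities on department and the "deprivation group (according to the FDep) makes it possible to randomly assign one of the 6 research" groups. No cut-point is given at that place.

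**Both draws.** Section 8.2.1 says "These 2 randomizations are stratified on the department and the ecological indicator of deprivation (FDep"), with FDep "dichotomized into 2 classes (< or > median of eligible municipalities in the department"). It adds "The 90 municipalities will be randomized concomitantly ('all at once").

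**Arm sizes.** Section 11.2: "we plan to include a total of 90 municipalities (15 per group").

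**Primary model.** Section 11.3.1: "The model will be a linear model in which we will consider 3 fixed effects (one per component) and potential interactions between component", and "The baseline VC will be considered as an adjustment variable". The longitudinal model for M2, M6 and M12 likewise names only baseline coverage as a covariate. FDep enters section 11.3.1 in descriptive breakdowns and in subgroup analyses with interaction terms.

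**Secondary objective 2.** Section 11.3.2 (ii) adds FDep as an adjustment variable to the multivariate regression models and refers the reader to 10.3.1. Section 10.3 is the data circuit and has no subsection 10.3.1; section 11.3.1 is apparently meant.

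**The concern.** A stratified draw can be reproduced and reported only if the strata are defined once. With two cut-points, the protocol does not say which municipalities shared a stratum, for the draw already made or for the allocation still to come.

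Stratifying on deprivation and geography treats these as likely predictors of uptake. An analysis that leaves them out gives up part of the benefit. Balance achieved in the draw is not credited in the standard error, and imbalance left by chance is not corrected in the realised estimate. With 90 clusters as the units of analysis, precision is worth having, and the data are already collected: section 10.1 lists department and FDep for every participating municipality.

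**Working it through.** **1. The cut-points side by side**

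| Draw | Section 5.3 | Section 8.2.1 |
|---|---|---|
| Selection of 409 | national average | department median |
| Allocation of 90 | deprivation group, no cut-point | department median |

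Take a department whose eligible municipalities all lie above the national average. The first rule puts them all in one class; the second splits them in half. More generally, where the department median is above the national average, every municipality between the two values is in the upper class under section 5.3 and in the lower class under section 8.2.1.

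For the selection draw the contradiction is direct. For the allocation it arises if the undefined deprivation group is read back to the definition given earlier in section 5.3, which is the natural reading but not a certain one.

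**2. The planned 15 per group reproduces**

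Inputs from section 11.2: 7.86% against 17.86% (the 10% increase read as percentage points), mean cluster size 466, coefficient of variation 0.5, intra-class correlation 0.05, power 90%, alpha 5%; two-sided from section 11.3.1.

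- Individuals per group without clustering: 234 (pooled variance) or 230 (unpooled).
- Design effect: 1 + ((0.5² + 1) × 466 − 1) × 0.05 = 30.08.
- Clusters per group: 234 × 30.08 / 466 = 15.1, or 14.9 unpooled. Power with 15 per group is 89.9%.

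The sample size is not in question.

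**3. What adjustment could gain**

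Let R² be the share of the underlying between-municipality variance, after baseline coverage, that FDep class and geography explain. The documents give no value, so 0–30% is an assumed range. The ratio of adjusted to unadjusted standard error is about √(1 − R²):

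| R² | Ratio | Reduction in SE |
|---|---|---|
| 0 | 1.000 | none |
| 0.10 | √0.90 = 0.949 | 5% |
| 0.30 | √0.70 = 0.837 | 16% |

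This ignores the degrees of freedom spent. With the six arms fitted in full (5 parameters), an intercept and baseline coverage, 90 − 7 = 83 residual degrees of freedom remain. FDep class (1) and 14 academies as fixed effects (13) leave 83 − 14 = 69.

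**4. Size of the allocation strata**

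The number of departments is not stated. Assuming at least one per academy, the 14 academies of section 4.1 give at least 14 × 2 = 28 strata, so at most 90/28 = 3.2 municipalities per stratum for six arms. With 20, 30 or 45 departments the average is 2.25, 1.5 or 1.0. An average of six would need at most 90/6 = 15 strata, hence at most 7 departments.

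If every stratum were allocated on its own (simulated with equally likely strata), the gap between largest and smallest arm would average about 6 municipalities at 28 strata and about 8 at 60. If the remainders run on from one stratum to the next, the draw is 15 complete blocks of six, and every arm receives exactly 15.

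**The case against.** **The cut-point conflict touches only the completed selection draw.** The national average is stated only for that draw, and section 8.2.1 gives an explicit rule for the allocation. This has force: the direct contradiction is confined to selection. But section 5.3 describes the allocation strata without a rule of its own, so a reader of that section would carry the national average forward. The sections still have to be reconciled.

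**FDep is in the models.** Section 11.3.2 (ii) adds it, and section 11.3.1 uses it in interactions. It would therefore be wrong to infer that FDep is left out of the analysis altogether. What stands is that the main primary model does not name it, the link for secondary objective 2 points to the wrong place, and department is in no model.

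**Covariates belong in the analysis plan, and baseline coverage absorbs these factors anyway.** The protocol does not leave covariates open; it names one. Baseline coverage of the same municipality may well absorb much of the regional and deprivation variation. It is weaker for boys, about 51% of the age group (100 − 48.85), whose baseline section 11.2 takes as 0%: baseline differences between municipalities then come from girls alone. How much is left to explain is unknown, which is why the range starts at no gain.

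**The strata are too fine, so the stratification fails.** A reader might infer this from 3.2 municipalities per stratum and the arm-size gaps above. The documents do not support it. Those gaps assume separate allocation of each stratum, which the protocol does not state, and a number of departments that it does not give. Fifteen per group is fixed and all 90 are drawn together, so remainders can be carried over. Even separate allocation does better than none: at 28 strata the FDep share differs by about 22 points between extreme arms, against about 32 without stratification and about 6 with remainders carried over. Coarser strata or constrained randomisation would be a design preference.

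**Conclusion.** The concern holds for two things. The protocol gives two FDep cut-points that must be reconciled, and the primary model as written omits the factors on which the allocation is stratified: department entirely, and FDep except in subgroup and secondary analyses.

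It does not follow that the primary result would be biased. Under randomisation the omission costs precision, tends to leave the standard error conservative, and leaves chance imbalance unadjusted. The size is conditional: 5–16% off the standard error if the factors explain 10–30% of the variance after baseline, and nothing if they explain nothing. No figure in the protocol fixes where in that range the trial lies.

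The small strata call for one stated detail, the handling of remainders. They are not evidence that the six-arm comparison is unprotected.

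**What to change.** - **Cut-point.** Record the FDep rule actually used to draw the 409 municipalities. State one rule for the allocation, in the same words in sections 5.3 and 8.2.1. Cost: wording. A footnote in section 5.3 says that the list of participating municipalities is not yet established, so on the protocol's own account the allocation is still ahead.
- **Models.** In section 11.3.1, add the FDep class used for allocation, and geography, to the primary model and the M2/M6/M12 model. Geography can be academy as a fixed effect, or department as a random effect because strata are small. Cost: no new data; with academy fixed, 14 of the 83 residual degrees of freedom. If that is thought too many, the random effect is the more economical choice.
- **Cross-reference.** In section 11.3.2 (ii), replace 10.3.1 by the intended section, and say whether FDep adjustment belongs to the primary model or only to secondary objective 2.
- **Remainders (secondary).** State in section 8.2.1 that incomplete strata are carried over within the single draw so that each arm receives 15. Cost: one sentence and, if needed, a change to the allocation program before it is run.

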### **8.2.2. Authorized and prohibited treatments during research including rescue treatments**

No treatment is prohibited during research.

During the half-days of vaccination on the middle school sites, the teams (doctor and nurse) from the vaccination center will travel with a first aid kit, containing medications and medical devices allowing them to deal with a possible anaphylactic or other reaction. adverse event considered 'serious'. The severity and appropriate management of the event will be left to the discretion of the vaccination center doctor.

## **9. SAFETY**

### **9.1. Definitions**

An adverse effect is defined as any harmful and unwanted manifestation likely to be linked to the handling or consumption of a product, a substance or occurring during an act of care.

An adverse reaction meets the definition of "serious" if it:

- causes death;
- endangers the life of the participant (effect during which the subject risked death; it does not designate an event/effect which hypothetically could have caused death if it had been more serious);
- requires hospitalization or extension of hospitalization;
- causes significant or lasting disability or incapacity;
- results in a congenital anomaly or malformation;
- is a "significant medical event" (event considered by the investigator to be medically important and which may endanger the subject or require intervention, medical or surgical, to prevent one of the characteristics/consequences mentioned above. Examples: treatment intensive care in hospital emergency rooms or at the research participant's home for allergic bronchospasm, seizure or coagulation disorders).

## **9.2. Responsibilities of the investigator**

The investigator immediately declares to the sponsor any serious adverse effect likely to be linked to the research procedures and any new fact, that is to say any new safety data which may lead to a reassessment of the benefit/risk ratio of research, or which might be sufficient to consider changes to the research documents.

To do this, he must immediately send a copy of the document detailing the circumstances of the serious adverse effect or the new fact to the [[contact]](mailto:[contact])

Any other adverse effect likely to be linked to a product taken by the participant must be declared by the investigator to the competent structures in accordance with the applicable regulations (<http://social-sante.gouv.fr/grands-dossiers/signalement-sante-gouv-fr> in France).

